### Intervention

Each participant will attend 3 one-week-long assessments in their respective schools, where we will assess their habitual sleep patterns and endogenous melatonin level before the intervention (T1), in the mid of the study (5 weeks after the commencement of the study) (T2) and after the 10-week intervention (T3). The mid-assessment is valuable to know how much variance in sleep behaviors is accounted by variance in melatonin, as well as to assess the adherence of the interventions. SPIRIT schedule of the study and a flow diagram of the study are shown in Figs 1 and 2 respectively. The estimated starting date of the study will be 1^st^ August, 2022 and the estimated ending date will be 30^th^ June, 2023.

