### Sample size calculation

Previous study [13, 14] showed physical exercise had notable effects (corresponding to a Cohen’s *d* of about 0.9) on improving sleep onset latency, sleep duration and sleep duration. We assumed that melatonin supplements have similar effects on sleep. A sample of 20 participants per group is computed by G*power software to achieve a power of 80% and a level of significance of 5% and 95% confidence level. Assuming 25% attrition rate, 25 participants per group will be recruited (i.e. the total number is 100).

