### Statistical methods

All statistical analyses will be conducted using SPSS (version 26.0) for Windows (SPSS Inc., Chicago, IL, USA). All the data will be entered into SPSS by the research assistant. One-way (4 Groups: physical exercise vs melatonin supplement vs combined exercise and melatonin supplement vs placebo-control) analysis of variances (ANOVA) with repeated measures will be performed to compare changes in actigraphy data and endogenous melatonin level between and within groups over different time points (i.e. T1-T3). Post-hoc analyses will be performed when any significant difference both between- and within-group is found in any of the outcome variables. Bonferroni correction will be used to adjust the alpha levels. Depending on the proportion of missing data and the assumption of normality, multilevel regression or a generalized estimating equation (GEE) will also be used as a sensitive analysis to assess the effects of the physical exercise intervention, melatonin supplement, time effect, and their interaction with sleep outcomes and melatonin level outcomes if there is any missing data. Average time spent in both daily sedentary activity and MVPA at baseline will be used as covariates. Linear regression will be used to analyse the association between participant’s adherence to the intervention and the outcome variables as a secondary analysis. Mediation analysis will be conducted to examine the mediating effect of endogenous melatonin level at T2 on the relation between physical exercise and sleep at T3. Preacher and Hayes’ bootstrapping and conditional process modeling will be used to determine the significance of the mediating effect. A p-value of <0.05 will be considered statistically significant. Both proposal analysis and intention-to-treat analysis will be carried out. Demographic variables (e.g. age, sex, BMI) will be adjusted if they demonstrate clinically significant prognostic effects on the outcomes (with absolute correlation or Cohen’s d effect size of >0.2) for both main analysis and mediation analysis.

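### The T1 value of each sleep and melatonin outcome is only a repeated level, never a covariate, so comparisons of change lose precision that data already collected could supply

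*Protocol article*

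**What the plan says.** The protocol article, Statistical methods, specifies that a four-group "analysis of variances (ANOVA) with repeated measures will be performed to compare changes in actigraphy data and endogenous melatonin level", with T1, T2 and T3 as the time points. T1 precedes the intervention, T2 falls at five weeks and T3 follows the ten-week programme (Intervention section). T1 is therefore one level of the repeated outcome.

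If data are missing, "multilevel regression or a generalized estimating equation (GEE) will also be used as a sensitive analysis". The next sentence gives the activity covariates: "Average time spent in both daily sedentary activity and MVPA at baseline will be used as covariates". Later in the section, "Demographic variables (e.g. age, sex, BMI) will be adjusted if they demonstrate clinically significant prognostic effects on the outcomes", with a threshold of 0.2 for the absolute correlation or Cohen's d.

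Nowhere does the section make the T1 value of a sleep measure, or of urinary aMT6s, a covariate. Nor does it constrain arm means to be equal at T1.

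**The concern.** A child's own T1 sleep, recorded with the same device ten weeks earlier, is likely to predict T3 sleep better than T1 activity, age, sex or BMI. The plan has a rule for adding prognostic variables but confines it to demographic ones. With T1 as a level of the outcome, the group-by-time contrast between T3 and T1 is a change-score comparison. For a given chance gap at T1, a change score over-corrects, by (1 - r) times the gap.

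The first objective is to find which intervention works better. That rests on contrasts between arms of about 20 children each, so lost precision matters.

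**Working it through.** **Inputs from the protocol (Sample size calculation):** d about 0.9, 80% power, 5% significance, 20 evaluable per arm. Two-sided testing is assumed. **Not in the protocol:** the T1-T3 correlation r, any SD, and the scale of d. I take r from 0.3 to 0.9 and equal variances at T1 and T3.

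**The plan's own figure.** n = 2 × ((1.96 + 0.84)/0.9)² = 19.4, so 20 per arm is reproduced. The exact t calculation gives 79.2% power at 20 per arm and requires 21.

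**Variance.** In units of the outcome variance, the change T3 - T1 has variance 2(1 - r), and T3 adjusted for T1 has 1 - r². The ratio of adjusted to change is (1 + r)/2. The reduction from adjusting is 1 - (1 + r)/2, and the excess from not adjusting is 2/(1 + r) - 1.

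| r (assumed) | Change 2(1 - r) | Adjusted 1 - r² | Variance cut by adjusting | Excess variance of change | Excess SE of change |
|---|---|---|---|---|---|
| 0.3 | 1.40 | 0.91 | 35% | 54% | 24% |
| 0.5 | 1.00 | 0.75 | 25% | 33% | 15% |
| 0.7 | 0.60 | 0.51 | 15% | 18% | 8% |
| 0.8 | 0.40 | 0.36 | 10% | 11% | 5% |
| 0.9 | 0.20 | 0.19 | 5% | 5% | 3% |

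A simulation with 20 per arm gave excess variances of 32% at r = 0.5 and 15% at r = 0.7. These are slightly below the formula because the adjusted analysis must estimate a slope.

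**Power.** Noncentral t, 20 per arm, 0.9 taken as a difference in T3 SD units, pooled error df 76 (75 with the covariate). The six-pair Bonferroni level, 0.05/6, is an assumption, since the plan does not give the number of comparisons.

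| r | Change, 5% | Adjusted, 5% | Change, 0.05/6 | Adjusted, 0.05/6 |
|---|---|---|---|---|
| 0.3 | 66% | 84% | 39% | 61% |
| 0.5 | 80% | 90% | 56% | 72% |
| 0.7 | 95% | 98% | 83% | 90% |
| 0.8 | 99.3% | 99.7% | 96% | 98% |

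At r = 0.5 the 95% CI half-width is 0.63 SD for change and 0.55 SD adjusted.

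**Chance baseline gaps.** The gap between two arms of 20 has standard deviation √(2/20) = 0.32 SD. A given pair differs by more than 0.5 SD in 11% of trials; the largest gap among four arms does so in 39%. At r = 0.5, a 0.5 SD gap moves the change contrast by (1 - 0.5) × 0.5 = 0.25 SD. In the simulation, the slope of the estimate on the gap was -0.50 (r = 0.5) and -0.30 (r = 0.7) for change, and about zero with adjustment. Both estimators averaged the true 0.9.

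**The case against.** Repeated-measures ANOVA with T1 as a level is a standard, valid analysis, and the section contains no contradiction on this point. That stands: this is a gain in efficiency, not the repair of an error. Four further points limit the case.

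- **Size.** The gain depends on an unknown r. Sleep is recorded over seven days per assessment, so r above 0.7 cannot be excluded, and there the benefit is small.
- **Contrast.** The plan does not say whether post-hoc tests compare change or means at a visit. If arms are compared at T3 alone, the variance is 1 rather than 2(1 - r), and the change-score figures do not apply (the two coincide at r = 0.5). Adjustment still helps, because 1 - r² is below 1.
- **Scale of d.** If 0.9 is on the change scale, change-score power is about 80% at every r. A reader might infer from the 66% or 39% above that the trial is underpowered for this reason; the protocol does not support that, as it gives neither r nor the scale of d.
- **Missing T1.** Nights with too little wear are excluded, so some children may lack a valid T1. A T1 covariate in the multilevel/GEE model would drop them, although that model is there to handle missing data.

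Two stronger readings are tempting. One is that chance baseline gaps bias the results. Under randomisation both estimators are unbiased and the standard error already reflects such gaps, so this is the same precision loss seen conditionally. The other is that the main ANOVA adjusts for activity but not for baseline sleep. The activity sentence directly follows the multilevel/GEE sentence and may belong only there. T1 outcome adjustment is absent on either reading.

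Detailed model specification is often left to an analysis plan. Here, however, the article chooses the model and names covariates, so it is fair to comment on what that choice leaves out.

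**Conclusion.** The point holds as a recommendation on efficiency. The named covariates omit the T1 outcome in both models, and T1 adjustment is more precise than change for every r below 1. For T3 - T1 contrasts the excess variance of change runs from 54% at r = 0.3 to 5% at r = 0.9, and the excess SE from 24% to 3%. The gain in power is useful at moderate r and negligible in the upper part of the range. These sizes rest on assumed r, equal variances and a change contrast; the power figures also need d in T3 SD units. The consequence is wider intervals and sensitivity to chance baseline gaps, without systematic bias.

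**What to change.** - **Main analysis.** For each sleep and melatonin outcome, model T2 and T3 with group, time and group-by-time, and add the T1 value of the same outcome as a covariate. Report T1-adjusted arm differences at T3 with 95% CIs.
- **Multilevel/GEE sensitivity analysis.** Keep T1 as an outcome with T1 means constrained equal across arms, or otherwise retain children without a valid T1, so that no child is dropped.
- **Activity covariates.** State whether baseline sedentary time and MVPA enter the main model, the sensitivity model or both.

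The cost is analysis wording and one degree of freedom in the main model. T1 assessments are already scheduled, so no new data are needed.

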Over the past decade, a significant body of research has investigated the effects of physical exercise on sleep and the results generally supported the positive impact of physical exercise on sleep (see Kelley et al. [12] for review). Previous studies also support the sleep benefits of physical exercise in children with ASD. For example, we have examined the impact of a basketball training intervention on sleep quality (sleep efficiency and wake after sleep onset) and cognition (inhibition control and working memory) in 40 children with ASD [13]. Research revealed a significant improvement in sleep efficiency and reduction in wake after sleep onset time in the intervention group but not in the control group [13]. Similar sleep benefits following physical exercise were also evident in a more recent study [14], where we showed that jogging intervention had significantly improved sleep efficiency and sleep duration in children with ASD. More remarkably, we also observed that the endogenous melatonin level, as reflected by the 6-sulfatoxymelatonin (aMT6s), was significantly increased within the jogging intervention group, while no change was found in the control group. Physical exercise appears to be capable of modulating the endogenous melatonin level in children with ASD, which in turns improves their sleep quality. If it is so, it is then natural to ask which intervention (i.e. physical exercise or melatonin supplement of the combination of two) is more effective in treating sleep disturbance improving the sleep quality of children with ASD. Without direct comparison, this question remained unanswered. Therefore, here we propose a new study protocol.

This study protocol has two objectives: (1) to determine which intervention is more effective in improving sleep quality in children with ASD and 2) to explain how these interventions impact on sleep via melatonin-mediated mechanism model. We hypothesise that the combination intervention (i.e. jogging and melatonin supplement) is the most effective because it may provide sufficient melatonin level to enhance sleep quality through both physical exercise and melatonin supplement.

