### Study measures

The demography and developmental history of each participant will be obtained from their parents or schools. And the following measurements will be carried out at T1, T2 and T3.

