## Discussion

This study protocol is designed largely based on our previous protocol and study [14, 17] that showed urinary melatonin level in children with ASD could be affected by their physical exercise participations. The study takes one-step forward by further comparing the efficacy of physical exercise and melatonin supplement intervention on treating sleep disturbance in children with ASD. The findings of the study will have three significant impacts. First, if the three interventions were equally effective, then physical exercise, which is more naturalistic and brings other health benefits, can be an alternative option for practitioners and parents to treat sleep problems for their patients and children with ASD. Second, if there was a difference between the three interventions on treating sleep problems, it will then inform further research on the relationship between physical exercise, melatonin supplement and sleep. For example, if the combination was the most effective intervention to ameliorate the sleep disturbance in children with ASD, it would imply researchers may need to further investigate other factors such as neurological factors (e.g. brain derived neurotrophic factor) or psychological factors (e.g. happiness, motivation) that may play a role on mediating the relationship between physical exercise and sleep. Third, this study enables the investigators to follow up their previous study, where they were investigating the melatonin-mediated mechanism between physical exercise and melatonin. The findings of this study will allow the investigators to reaffirm if melatonin mediates the relation between physical exercise and changes in sleep quality, which would further strengthen the current limited evidence on the efficacy of physical exercise for sleep problems in children with ASD. The findings of the proposed study will ultimately lead to optimal treatment interventions for sleep disturbance not only in children with ASD, but also in any population suffering from sleep disturbances.

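### The mediation model names no T1 melatonin or T1 sleep covariate, so stable differences between children could be read as mediation

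*Protocol article*

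**What the plan says.** The second objective in the Introduction is "to explain how these interventions impact on sleep via melatonin-mediated mechanism model". The Statistical methods section gives the analysis for it: a model to "examine the mediating effect of endogenous melatonin level at T2 on the relation between physical exercise and sleep at T3", where "bootstrapping and conditional process modeling will be used to determine the significance of the mediating effect".

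Two statements on adjustment follow or precede this:
- Demographic variables (age, sex and BMI are the examples) are adjusted when their correlation or standardised difference exceeds 0.2, "for both main analysis and mediation analysis".
- "Average time spent in both daily sedentary activity and MVPA at baseline will be used as covariates", with no statement of which model this applies to.

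Neither list contains T1 melatonin or T1 sleep. Both exist: under Study measures, "the following measurements will be carried out at T1, T2 and T3", and sleep and aMT6s are the primary outcome measures listed there. The Discussion says the result will show whether "melatonin mediates the relation between physical exercise and changes in sleep quality", which concerns change, whereas the model as worded has sleep at T3 as its outcome.

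**The concern.** An indirect effect is the product of two paths. Randomisation protects the first, exercise to melatonin. It does not protect the second, melatonin to sleep, because no one randomises a child's melatonin level within an arm. A child who habitually has low aMT6s and habitually sleeps badly contributes to a T2-to-T3 association whether or not a change in melatonin alters sleep. The bootstrap describes the sampling error of the product; it does not remove that confounding.

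At stake is the mechanistic conclusion. The article intends to use this result to reaffirm that melatonin carries the effect of exercise on sleep. The between-arm comparison of sleep, which answers the first objective, is not affected.

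**Working it through.** **The plan's own figure.** The article gives no sample size for the mediation analysis. Its only calculation is 20 per group for d = 0.9, 80% power and 5% significance. Normal approximation: 2 × (1.960 + 0.842)² / 0.9² = 15.70 / 0.81 = 19.4, so 20. The figure reproduces (power with the t distribution is 79.2%). I use 20 versus 20 below.

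**Inputs.**
- From the article: 20 evaluable per group; effect on sleep 0.9 SD; 5% significance (taken as two-sided); a positive exercise effect on melatonin is expected from the earlier jogging study, but no size is given.
- Assumed, because the article gives no figure: exercise effect on T2 melatonin, a = 0.3, 0.5 or 0.9 SD; baseline melatonin–sleep correlation between children, r = 0 to 0.5; stability over time 0.75.
- Melatonin has no effect on sleep, so the true indirect effect is 0.

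**Why the estimate is not zero.** Let X be exercise, and let the within-arm SDs be 1:
- T2 melatonin = stable child component + a·X + error
- T3 sleep = correlated stable child component + 0.9·X + error

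Regressing T3 sleep on X and T2 melatonin gives an expected melatonin coefficient of b = r. The apparent indirect effect is a × b:
- a = 0.3, r = 0.2: 0.3 × 0.2 = 0.06 SD
- a = 0.5, r = 0.3: 0.5 × 0.3 = 0.15 SD
- a = 0.9, r = 0.5: 0.9 × 0.5 = 0.45 SD, which is 0.45 / 0.9 = half of the assumed total effect on sleep

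**How often the test is then significant.** This is the share of simulated trials in which the bootstrap 95% interval for a × b excludes zero, with no T1 values in the model:

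| Exercise effect on melatonin | r = 0.2 | r = 0.3 | r = 0.5 |
|---|---|---|---|
| 0.3 SD | about 4% | about 9% | about 15% |
| 0.5 SD | about 7% | about 15% | about 37% |
| 0.9 SD | about 22% | about 40% | about 73% |

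At r = 0 the rate is about 5% or less. Across these settings, adding T1 aMT6s and T1 sleep to both equations gives about 1–12%, and using change from T1 for both variables gives about 1–9%.

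**Precision.** A separate run of 600 trials per setting gave 17% instead of 22% (0.9 SD, r = 0.2) and 29% instead of 37% (0.5 SD, r = 0.5). Read the table to within several percentage points.

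**Sensitivity.** A different set-up fixed the correlation of the stable components (0.3 to 0.7) and the intraclass correlation (0.5 to 0.9). The observed correlation is then their product, for example 0.7 × 0.7 = 0.49.
- If exercise does not move melatonin (a = 0), the unadjusted rate is at most 4.3% with 40 children and 6.7% with 80.
- With a = 0.9 SD and 40 children, it is 14–84% unadjusted, 6–13% with both T1 covariates and 5–7% with change scores.
- With a = 0.9 SD and 80 children (all four arms, exercise yes or no), it is 28–98%, 7–24% and 4–7%.

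So T1 covariates remove most of the bias but not all of it when a single T1 measurement is noisy. Change scores do well here partly because the simulation lets the stable component act equally at every visit.

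**The case against.** The strongest reply is that a condensed article leaves model details to an analysis plan that is not shown. No sentence says that unadjusted values will be used or that T1 is excluded, and the Discussion's reference to changes in sleep suggests that the authors have baseline in mind. This stands in part: a reader might infer that T1 values have been deliberately left out, and the text does not say so. But the article does more than stay silent. It fixes the mediator, the outcome, both time points, the test and the covariates, and T1 aMT6s and T1 sleep are not among those covariates. Followed as written, the model is confounded.

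A second reply concerns plausibility. A reader might take the Introduction to argue that, among children with ASD, those with lower melatonin sleep worse. It does not. It reports lower melatonin production in children with ASD than in typically developing peers, which is a difference between populations. The eligibility limits (age 8–11, Tanner stage I, SRS T-score of 80 or above, reported sleep-onset delay) may also weaken any such correlation. This stands: the correlation is an assumption.

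Third, the 0.9 in the sample size section concerns sleep, not melatonin. Using it for the exercise-to-melatonin path gives the top of the range, and smaller effects give much smaller error rates. This also stands, and is why the full range is shown.

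**Conclusion.** The point holds in conditional form. As worded, the mediation model can declare mediation when melatonin has no effect on sleep. This requires both that exercise raises melatonin, which the protocol expects, and that melatonin and sleep are stably correlated between children, for which the documents give no figure. Without either condition, the error rate stays close to the nominal level. With both, it runs from no inflation (about 4%) to about 73% with 20 versus 20 children, depending on assumed values.

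Two stronger readings are not supported. One is that the trial would report false mediation: that needs a correlation and a melatonin effect of a size the article does not state. The other is that the model compares the jogging arm alone with control: the text names only physical exercise as the predictor and does not say which arms enter. That is a separate question and not part of this point.

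**What to change.** In the mediation analysis, include T1 aMT6s and the T1 value of the sleep outcome as covariates in both the mediator and the outcome equation. Alternatively, define both variables as change from T1 (T2 minus T1 for melatonin, T3 minus T1 for sleep), which matches the aim stated in the Discussion. Choose one before unblinding and name it. Add that neither approach removes unmeasured confounding that varies over time, so a significant indirect effect would support the melatonin mechanism without establishing it.

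The cost is a sentence or two of wording. Both T1 measurements are already scheduled. The covariate version uses two degrees of freedom, out of about 40 children if two arms are compared.

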## Discussion

This study protocol is designed largely based on our previous protocol and study [14, 17] that showed urinary melatonin level in children with ASD could be affected by their physical exercise participations. The study takes one-step forward by further comparing the efficacy of physical exercise and melatonin supplement intervention on treating sleep disturbance in children with ASD. The findings of the study will have three significant impacts. First, if the three interventions were equally effective, then physical exercise, which is more naturalistic and brings other health benefits, can be an alternative option for practitioners and parents to treat sleep problems for their patients and children with ASD. Second, if there was a difference between the three interventions on treating sleep problems, it will then inform further research on the relationship between physical exercise, melatonin supplement and sleep. For example, if the combination was the most effective intervention to ameliorate the sleep disturbance in children with ASD, it would imply researchers may need to further investigate other factors such as neurological factors (e.g. brain derived neurotrophic factor) or psychological factors (e.g. happiness, motivation) that may play a role on mediating the relationship between physical exercise and sleep. Third, this study enables the investigators to follow up their previous study, where they were investigating the melatonin-mediated mechanism between physical exercise and melatonin. The findings of this study will allow the investigators to reaffirm if melatonin mediates the relation between physical exercise and changes in sleep quality, which would further strengthen the current limited evidence on the efficacy of physical exercise for sleep problems in children with ASD. The findings of the proposed study will ultimately lead to optimal treatment interventions for sleep disturbance not only in children with ASD, but also in any population suffering from sleep disturbances.

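### The Discussion names equal effectiveness of the three interventions as a possible conclusion, but the planned group comparisons test only for differences, and about 20 children per arm cannot show equality

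*Protocol article*

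**What the plan says.** The aim in the Introduction is comparative: "to determine which intervention is more effective in improving sleep quality in children with ASD". The hypothesis is one of superiority: "We hypothesise that the combination intervention (i.e. jogging and melatonin supplement) is the most effective". No hypothesis of equivalence or non-inferiority is stated.

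Under Sample size calculation, a Cohen's d of about 0.9 is taken from earlier exercise studies. The text adds: "We assumed that melatonin supplements have similar effects on sleep". This leads to 20 per group, raised to 25 for 25% attrition.

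Under Statistical methods, "analysis of variances (ANOVA) with repeated measures will be performed to compare changes in actigraphy data and endogenous melatonin level". Pairwise work is conditional: "Post-hoc analyses will be performed when any significant difference both between- and within-group is found in any of the outcome variables". Bonferroni correction applies, but the number of comparisons is not given. The significance rule is "A p-value of <0.05 will be considered statistically significant". A multilevel or GEE model is a sensitivity analysis that depends on missing data and normality. Adherence regression and mediation analysis are also planned.

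The Discussion then says what the results would mean. The first reading is "if the three interventions were equally effective, then physical exercise, which is more naturalistic and brings other health benefits, can be an alternative option". The second begins "if there was a difference between the three interventions on treating sleep problems". It gives no reading for an inconclusive comparison.

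**The concern.** A conclusion of equal effectiveness needs evidence that any difference is smaller than some stated amount. A difference test does not give that evidence. A non-significant p-value can come from a true difference near zero or from an imprecise estimate. Here the sizing assumes similar effects for melatonin and exercise, so the assumed head-to-head difference is about zero and no contrast between active arms was powered. A non-significant jogging-versus-melatonin result is therefore what the design leads one to expect.

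The Discussion addresses the equality reading to practitioners and parents. If it were reached from a non-significant comparison, they could take jogging to match melatonin although the data were compatible with a much smaller effect.

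**Working it through.** **Inputs from the protocol.** d = 0.9; power 80%; alpha 5% (taken as two-sided); 20 per group; 25 recruited with 25% attrition; equal allocation.

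**Assumptions, not in the protocol.** Bonferroni over 3 pairs (active arms only) or 6 pairs (all four arms); a baseline correlation of 0.5 for the adjusted case; a scenario in which jogging has half of melatonin's effect, so the difference is 0.9 / 2 = 0.45 SD.

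**1. The plan's own figure.** n = 2 × ((1.960 + 0.842) / 0.9)² = 19.4, so 20 per group. The exact t-test needs 21 and has 79.2% power at 20. The stated 20 is thus reproduced as a two-group superiority test of d = 0.9 at an unadjusted two-sided 5%. After the stated attrition, 25 × 0.75 = 18.75 per group remain.

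**2. Precision of jogging minus melatonin.** Half-width in SD units = t(0.975, 2n − 2) × √(2/n).

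| Case | Half-width (SD) | Share of 0.9 |
|---|---|---|
| n = 20, unadjusted | 0.640 | 71% |
| n = 18.75, unadjusted | 0.663 | 74% |
| n = 20, baseline-adjusted, correlation 0.5 | 0.555 | 62% |
| n = 20, Bonferroni, 3 pairs | 0.792 | 88% |
| n = 20, Bonferroni, 6 pairs | 0.880 | 98% |

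The adjusted row is √(1 − 0.5²) × t(0.975, 37) × √(2/20) = 0.866 × 0.641. With no attrition at all (n = 25) the unadjusted half-width is still 0.569 SD. At n = 20, an observed difference of exactly zero would therefore be compatible with jogging falling short by 0.64 SD.

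**3. Chance of missing a halved effect.** For a difference of 0.45 SD and n = 20, the noncentrality is 0.45 × √(20/2) = 1.42.

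| Level | Power | Non-significant |
|---|---|---|
| 0.05 | 28.4% | 72% |
| 0.05 / 3 | 15.3% | 85% |
| 0.05 / 6 | 10.0% | 90% |

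**4. Could another planned analysis support equality?** The multilevel or GEE model estimates effects of exercise, melatonin and time and their interaction. The adherence regression and the mediation analysis ask other questions. No margin or interval criterion is attached to any of them. If the overall ANOVA is null, the gate means that no pairwise estimate is planned. If it is significant, for example because the active arms beat placebo, the pairwise comparison is still a test for a difference.

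**5. What a margin would require.** For an illustrative margin of 0.45 SD and a true difference of zero, non-inferiority at one-sided 0.025 with 80% power needs 2 × ((1.960 + 0.842) / 0.45)² = 77.5, so 78 per arm. At 20 per arm the power is Φ(0.45 / √(2/20) − 1.960) = 30%. Placing the whole 95% interval inside ±0.45 SD with 80% power needs 2 × ((1.960 + 1.282) / 0.45)² = 103.8, so 104 per arm.

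**The case against.** The strongest reply is that the protocol never says that non-significance will be read as equality. The sentence is conditional, sits among possible impacts in a Discussion, and does not define how equality would be established. That is correct. A reader might infer a decision rule that turns a null result into a practice recommendation, or a plan to have jogging replace melatonin. The text supports neither: it says only that exercise can be an option. What remains is that the Discussion offers two readings and the plan supplies no evidence that could support the first.

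A second reply is that difference tests suit the stated aim of finding the more effective intervention. This also stands. The point is not that the main analysis is wrong for its objective, nor that ANOVA and post-hoc tests are the only analyses. The mismatch lies between the design and one stated conclusion.

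Third, exercise could fairly be called an option if it beat placebo, and the trial has a placebo arm. That is true, but it would not support a claim of equal effectiveness.

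Fourth, the size depends on assumptions. A reader might conclude from the Bonferroni rows that the interval always spans nearly the whole effect. That holds only if six pairs are counted, and the protocol does not give the number. The scale of d = 0.9 (raw or change) is also not stated. The imprecision remains with no multiplicity adjustment, and under the assumed baseline adjustment.

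Finally, a separate analysis plan may set interval reporting or a margin. Interval reporting would help, but a margin set later would not make 20 per arm adequate for one as small as 0.45 SD.

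**Conclusion.** The concern holds in this limited form: equal effectiveness is a stated possible conclusion, no planned group comparison can establish it, and the arm size is too small for the data to do so at any margin well below the assumed effect. The unadjusted 95% half-width is 0.64 to 0.66 SD, or about 0.55 SD with an assumed baseline correlation of 0.5. That is roughly 62 to 74% of the assumed 0.9 SD. A true halving of the effect would go undetected in about 72% of trials unadjusted and 85 to 90% under Bonferroni for three to six pairs. These figures assume 18.75 to 20 evaluable children per arm (20 for the halved effect and the adjusted half-width), two-sided testing and effects in SD units.

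This should be corrected, but it does not undermine the superiority comparisons. They remain usable for the stated objective.

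**What to change.** Make three changes of wording in the protocol, carried into any analysis plan:

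- Report the jogging-minus-melatonin difference with its 95% confidence interval in every case, whatever the overall ANOVA shows, so that this estimate is outside the post-hoc gate.
- State that a non-significant head-to-head comparison is inconclusive.
- Remove equal effectiveness as a conclusion. Alternatively, allow it only if the 95% interval lies within a justified margin fixed before unblinding for one named sleep outcome. The outcome must be named because four actigraphic sleep parameters are listed as primary without ranking.

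A statement that exercise is an option can rest on jogging versus placebo, provided it makes no claim of equality with melatonin.

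The changes need no extra participants or procedures. The cost is in what can be claimed: with a half-width of about 0.64 SD, even an estimate of zero would not bring the unadjusted interval inside a margin smaller than that, so the trial will probably be unable to claim equality. Keeping equality as a real aim would mean sizing for it, for example 104 evaluable per arm for a two-sided margin of 0.45 SD, which is an illustrative value.
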